### Methods

#### Trial design

The study employs the Standard Protocol Items Recommendations for Interventional Trials (SPIRIT) [40] as the reporting guideline for this protocol and adheres to Consolidated Standards of Reporting Trials (CONSORT) [41] to ensure quality in study planning, implementation, and reporting.

Figure 1 and Table 1 show the study procedure and the setup of the randomised control trial. This is a 3-arm stratified randomised controlled trial, with four groups distributed across two variants of the spiritual meditation condition (Christian and Islamic), MBSR, and a waitlist control condition. Participants will be first stratified into Christian and Muslim samples and then randomly allocated to one of the three conditions. Individuals assigned to the spiritual meditation condition will be further stratified into either a Christian or an Islamic contemplation subgroup within the spiritual meditation condition based on their religious affiliations.

Participants in the spiritual meditation groups and the secular mindfulness group will receive 8-week interventions, commencing with an initial face-to-face meeting, where they will practice the first session of the guided meditation course using the mobile app. Following that, they will continue with daily guided practices lasting approximately 20 min through the app. Assessment will be held at three time points including pre-intervention (T1, baseline), after the 8-week intervention (T2), and three months after the intervention (T3). Participants in the waitlist control group will only attend the assessments at T1 and T2, as due to ethical reasons they will be given the option to start using the Christian or Islamic meditation App after testing at T2.

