### Study interventions

The spiritual meditation interventions and MBSR will have the same structure and time frame. All interventions will be delivered through an initial face-to-face meeting, where participants will initiate the first session of the guided meditation course using the mobile app. Subsequently, they will continue with daily guided practices lasting approximately 20 min through the app over eight weeks. The initial meeting will start at the end of the baseline assessment (T1). Participants will only be able to access the app intervention that they are allocated to. Participants in the waitlist control group will not receive any types of intervention and will not attend the T3 assessment, but they will be given access to the Christian or Islamic meditation app version upon completion of the in-person T2 assessment.

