### Primary outcomes

The study is primarily assessing changes in interpersonal functioning, measured through prosociality, forgiveness, empathy, and perspective taking. Prosociality will be assessed at T1 and T2 via the *Dictator Game* (DG) [45], *Social Value Orientation* (SVO) [46], and *Charitable Giving* (at T2 only). Empathy and forgiveness variables will be collected via the task *Love thy Enemy* (adapted from Witvliet et al. [47]) at both T1 and T2. Perspective taking will be obtained online at T1, T2, and T3.

Dictator Game (DG) [45]: This computer-based task allocates ten game points to participants and asks them to decide how many of these points they would like to transfer to an anonymous participant. The outcome measure is the number of game points participants are willing to allocate to the anonymous individual. The game points retained by participants will have no influence on their real-life earnings or their compensation fee for taking part in the experiment. Prior studies have shown that individuals engage in prosocial activities irrespective of monetary incentives [48, 49]. 

Social Value Orientation (SVO) [46]: This online task consists of six items with which participants are asked to assign game points for themselves and an anonymous other. Participants will make their allocations by adjusting a slider to indicate their most preferred joint distribution between themselves and the other. A continuous social value orientation score will be computed from these six items based on participants’ choices. The outcome measure will be a single overall SVO score. A higher SVO score represents a higher prosocial preference. The game points kept by the participants will not affect their real-life earnings or their compensation fee for taking part in the experiment.

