### Secondary outcomes

Secondary outcomes encompass domains of physiology, attention, and mental health. Measures pertaining to the physiological and attention domains will be obtained at T1 and T2, while those related to mental health domain will be collected across all timepoints (T1, T2 and T3).

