### Analysis plan

#### Quantitative data

The analyses will follow both intention-to-treat principle and per-protocol principle, requiring a minimum completion of four days of meditation sessions per week over the 8-week intervention period and complete all required assessments. This study will consider a result with a p-value lower than 0.05 as statistically significant. A series of mixed-design Repeated Measures Multivariate Analysis of Variance (RM-MANOVA) will be used to test the mean difference in the outcomes among conditions (Spiritual meditation, mindfulness, and waitlist control groups) across T1, T2 and T3 as well as within participants across all time points (T1, T2 and T3). The specific prosociality variable, measured by Charitable Giving task, will be only compared between groups at T2. When justifiable, missing data will be imputed using multiple imputation of chained equations [68]. 

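### The stated RM-MANOVA compares three conditions over T1, T2 and T3, a layout that no primary measure has and that the waitlist cannot supply

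*Protocol article*

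**What the plan says.** **Analysis.** The Quantitative data section of the Analysis plan specifies mixed-design RM-MANOVAs to "test the mean difference in the outcomes among conditions (Spiritual meditation, mindfulness, and waitlist control groups) across T1, T2 and T3", plus within-participant comparisons over the same three time points. One exception follows: the prosociality variable "measured by Charitable Giving task, will be only compared between groups at T2". On gaps in the data the section says: "When justifiable, missing data will be imputed using multiple imputation of chained equations".

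**Waitlist schedule.** Trial design states: "Participants in the waitlist control group will only attend the assessments at T1 and T2". Study interventions adds that they "will not attend the T3 assessment, but they will be given access to the Christian or Islamic meditation app version" once T2 is complete, and Waitlist condition agrees.

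**Outcome schedule.** Primary outcomes begins its list of prosociality measures with "Prosociality will be assessed at T1 and T2 via the" and then marks Charitable Giving as T2 only. Forgiveness and empathy are collected "at both T1 and T2". Only perspective taking is also taken at T3. Under Secondary outcomes, "Measures pertaining to the physiological and attention domains will be obtained at T1 and T2", while the mental health scales run to T3. Table 2 agrees throughout.

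**Hypothesis and sample size.** Research question and hypotheses makes one directional between-arm prediction, spiritual meditation better than waitlist, and declines to predict the comparison with MBSR. Power analysis sizes the trial at 288 for four groups at three time points.

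**The concern.** The analysis section names the method, the conditions and the time points, and together they need a T3 value for every condition. The waitlist has none, and most primary measures have none in any condition.

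The comparison at stake is the one the trial makes a prediction about. For an outcome with a T3, a standard RM-MANOVA uses participants observed at all three times, so the waitlist drops out and the spiritual-versus-waitlist contrast goes with it. If someone tried to keep the waitlist by filling in T3, no observed waitlist T3 value would inform the imputation. By then waitlist participants may also be using the spiritual meditation app, so T3 would not be an untreated comparison. Because the stated model cannot be run as described, the analyst must choose another for the main hypothesis. If that choice is not fixed beforehand, it may be made after the data have been seen.

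**Working it through.** **Step 1. Stated layout against the schedule (Table 2, Primary outcomes, Trial design).**

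| Primary measure | Spiritual and MBSR | Waitlist | Three conditions by three times? |
|---|---|---|---|
| Dictator Game | T1, T2 | T1, T2 | No |
| Social Value Orientation | T1, T2 | T1, T2 | No |
| Forgiveness | T1, T2 | T1, T2 | No |
| Empathy | T1, T2 | T1, T2 | No |
| Perspective taking | T1, T2, T3 | T1, T2 | No |
| Charitable Giving | T2 | T2 | Not applicable: analysed separately at T2 |

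Of the five measures left in the RM-MANOVA, four have no T3 and the fifth has none in the waitlist. None of the five has the stated layout.

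**Step 2. Outcomes that do have a T3.** These are perspective taking, the DASS-21 subscales, WHO-5 and I-PANAS-SF. Take three equal arms of 288/3 = 96. Complete cases over T1-T3 are then at most 96 spiritual, 96 MBSR and 0 waitlist; over T1-T2 they are 96, 96 and 96. The article also gives 72 per group for four groups; on that count 72 of 72 waitlist participants are lost. The loss is 100% either way.

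**Step 3. Reproduce the stated sample size.** Inputs from Power analysis: k = 4 groups, m = 3 times, alpha 0.05, power 0.85, effect size 0.1, dropout 10%. Assumed, because not stated: correlation between repeated measures rho = 0.5, sphericity (epsilon = 1), and the within-between interaction test. The noncentral F test has

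- lambda = f² × N × m / (1 − rho)
- df1 = (k − 1)(m − 1), df2 = (N − k)(m − 1)

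With f = 0.1 and N = 260: lambda = 0.01 × 260 × 3 / 0.5 = 15.6, df = 6 and 512, power 0.854. Adding dropout gives 260/0.9 = 289, or 260 × 1.1 = 286, so the stated 288 is reproduced closely. Reading 0.1 as f² (f = 0.316) does not reproduce it: the same test then needs 32 before dropout. The sample size therefore appears to rest on the four-group, three-time layout.

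**Step 4. The layout that exists in every arm, T1-T2.** Same f, rho and alpha. Completers are 288 × 0.9 = 259, taken as 260, so lambda = 0.01 × 260 × 2 / 0.5 = 10.4.

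| Layout | df | Power at 260 | N for 0.85 | N with 10% dropout |
|---|---|---|---|---|
| 3 conditions, 2 times | 2, 257 | 0.827 | 279 | 279/0.9 = 310 |
| 4 groups, 2 times | 3, 256 | 0.772 | 312 | 312/0.9 = 347 |

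Range over the assumed rho at 260 completers: for 0.4, lambda = 0.01 × 260 × 2 / 0.6 = 8.67 and power is 0.75 (three conditions) or 0.69 (four groups); for 0.6, lambda = 0.01 × 260 × 2 / 0.4 = 13.0 and power is 0.90 or 0.87.

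**Step 5. The single contrast.** Spiritual versus waitlist at T1-T2, equal arms: 192 × 0.9 = 173 completers, lambda = 0.01 × 173 × 2 / 0.5 = 6.92, df = 1 and 171, power 0.744. With two times and rho = 0.5 this is a test of change with a standardised difference d satisfying d² × 86.5 / 2 = 6.92, so d = 0.4. Adjusting T2 for T1 instead multiplies the outcome variance by 1 − rho² = 0.75, whereas change has 2(1 − rho) = 1. With 86 completers per arm and d = 0.4, power is 0.857 with adjustment and 0.746 on change.

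**The case against.** The strongest reply is that this is loose wording in a condensed article. The section speaks of a series of models, Table 2 fixes the occasions for each outcome, and no model can use an occasion that was never scheduled. The natural reading for the Dictator Game, Social Value Orientation, forgiveness, empathy, physiology and attention is then three conditions by two times, which tests the hypothesis with the stated method. Layouts for each outcome may also stand in an analysis plan that is not shown.

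Part of this stands. The two-time reading is reasonable for outcomes without a T3. It does not help outcomes with a T3, where the text puts the waitlist and T3 in one model. Nor is this simple omission: the section makes an explicit timing exception for Charitable Giving and for nothing else, and the sample size uses three time points as well.

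A reader might infer four stronger things that the article does not support:

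- **That the trial cannot test its between-arm hypothesis.** T1 and T2 data are scheduled in all three conditions, and the T2 comparison of Charitable Giving tests it directly.
- **That waitlist T3 values will be invented.** Imputation is limited to missing data and to cases where it is justifiable. Visits never scheduled need not count as missing, and nothing says they will be imputed. The gap is that the article does not rule it out.
- **That intention-to-treat is broken for anyone who misses a visit.** Complete-case fitting is the usual behaviour of RM-MANOVA, not a stated rule, and imputation may cover sporadic gaps.
- **That five of six primary measures conflict with the model.** Charitable Giving is taken out of it, so the count is four of the remaining five without T3.

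**Conclusion.** Wrong as written, and repairable from data already planned. The stated three-condition, three-time model fits none of the five primary measures assigned to it. For outcomes with a T3, its complete-case form removes 100% of the waitlist and with it the spiritual-versus-waitlist contrast. These conclusions follow from the schedule, plus the usual complete-case fitting of RM-MANOVA.

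The power consequence is modest and conditional. At f = 0.1, rho = 0.5 and about 260 completers, the T1-T2 interaction has power 0.83 or 0.77 against the stated 0.85. Holding f at 0.1 while the number of time points changes is itself an assumption, since the same f need not describe the same difference in means. These figures should not be read as proof that the trial is underpowered: a higher correlation, or adjustment for T1, recovers the shortfall.

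**What to change.** 1. State that the primary between-condition test for each outcome is the three-condition comparison at T2 adjusted for the T1 value (T2 only for Charitable Giving), on all randomised participants, with spiritual meditation versus waitlist as the key contrast. Keeping RM-MANOVA but limiting waitlist comparisons to T1-T2 would also remove the contradiction; adjustment for T1 is preferred for its precision.
2. Limit T3 analyses to spiritual meditation versus MBSR, on the outcomes measured at T3.
3. State that waitlist T3 is absent by design and will not be imputed, and that multiple imputation applies only to scheduled assessments that were missed.
4. Restate the power for the T1-T2 layout and the chosen test, giving the assumed correlation and whether 0.1 is f or f².

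Cost: an amendment to the analysis and power sections before any analysis of outcomes by arm, with no new assessments. The trial gives up any T3 claim against the waitlist, which the design cannot support. It may have to report power slightly below 0.85 if it keeps the repeated-measures interaction at 288.

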**Discussion:**

This trial aims to test the effects of an app-based Christian and Islamic meditation, compared to secular mindfulness and a waitlist, using a randomised controlled trial. If the results yield positive outcomes, this study will support the efficacy of these contemplations, offering practitioners a way to enhance their well-being within their religious framework.

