## Research question and hypotheses

This study addresses the effects of heart-centred meditation from the Christian and Islamic traditions, compared to secular practices, on social functioning, physiology, cognition, and mental health. The key question is whether the regular practice of Christian or Islamic heart-centred contemplation fosters positive outcomes at the interpersonal and the individual levels, as compared to a standardised mindfulness-based stress reduction intervention (MBSR) and a waitlist control condition.

To address these questions, this study will develop (a) an 8-week intervention based on heart-centered Christian and Islamic contemplative practices; (b) a stratified 3-arm randomised controlled trial (RCT) with contemplations (Christian and Islamic), an active control (MBSR) and a waitlist control. The contemplation and MBSR programs will be delivered through a mobile app.

We hypothesise that when compared to baseline, individuals undertaking the heart-centred contemplative practices will show: (1) greater prosociality, forgiveness, empathy, and perspective taking; (2) increased pain tolerance and attention, and reduced subjective ratings of pain intensity, reduced stress reactivity as measured by HR and HRV, and reduced psychophysiological reactivity associated with forgiveness as measured by HR and HRV; (3) reduced self-reported stress, depression, anxiety; (4) increased subjective wellbeing and positive affect as well as reduced negative affect. We also hypothesise that these outcomes will be greater for participants in the heart-centred contemplations compared to those in the waitlist control condition. We have no specific predictions for comparing the outcome of the religious (Christian or Islamic) *versus* MBSR interventions.

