## Participants

### Power analysis

This study will recruit non-clinical samples of 144 Christian and 144 Islamic healthy adult participants. An a priori power analysis was conducted using the G*Power software (V.3.1) [42], considering four groups with mixed method repeated measures at three timepoints. The calculation was conducted based on a small effect size of *f*^*2*^ = 0.1, with an alpha value of 0.05, a desired power of β = 0.85. Effect size was set at 0.1 using a conservative approach due to the novel nature of the study to examine the effects of Christian and Islamic contemplation. Calculation was applied to determine the total sample size of 288 participants with (*n* = 72) per group, after adjusting for an estimated dropout rate of 10%.

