### Heart-centred spiritual meditations

The spiritual meditation programs were developed from techniques based on Christian and Islamic traditions. The primary elements of the practices consist of maintaining attention and emotional connection to God through visualisation and recitation. Concurrently these practices are expected to promote a moving away or transcendence from everyday concerns. Breathing is included as an added ingredient to help focus participants’ attention during the first part of each meditation. Although Christian and Islamic contemplations are typically not standardised within their respective contemplative traditions, for this study we had to develop specific scripts to be used by participants. These were developed by Christian and Islamic expert members of the research team, and subsequently edited by the lead researchers with the guidance of an expert in writing content for meditation Apps (see acknowledgements section).

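### The pooled spiritual-meditation contrast estimates the average of two programmes, so it cannot by itself support a claim about the Christian or the Islamic programme separately

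*Protocol article*

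**What the plan says.** All references are to the Protocol article.

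- **Analysis plan, Quantitative data.** A series of repeated-measures MANOVAs will "test the mean difference in the outcomes among conditions (Spiritual meditation, mindfulness, and waitlist control groups". Both programmes sit in the first of these three levels. The paragraph names no religion term, no condition-by-religion term and no contrast within a religion.
- **Research question and hypotheses.** The key question is "whether the regular practice of Christian or Islamic heart-centred contemplation fosters positive outcomes at the interpersonal and the individual levels". The hypotheses that follow concern the heart-centred practices as a group, against baseline and against waitlist. None is stated for one tradition alone.
- **Trial design.** The trial has three arms, "with four groups distributed across two variants of the spiritual meditation condition (Christian and Islamic), MBSR, and a waitlist control condition". Participants are divided by religion before randomisation, and religion alone fixes which spiritual programme a participant can receive (also in Randomisation and allocation).
- **Power analysis.** The size was found "considering four groups with mixed method repeated measures at three timepoints".
- **Heart-centred spiritual meditations.** On the scripts: "These were developed by Christian and Islamic expert members of the research team". The lead researchers then edited them.
- **Abstract, Discussion.** If results are positive, "this study will support the efficacy of these contemplations". The main Discussion adds that practitioners might then improve their well-being inside their own faith.

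**The concern.** The two programmes have different scripts and reach different people: no Muslim participant receives the Christian programme and no Christian the Islamic one. A single spiritual-meditation level therefore yields an average over two interventions in two populations. If the effects are similar, that average describes both. If they differ, it describes neither, and the test gives no sign of this.

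Two things are at stake. A significant pooled result could be taken as evidence for a programme that contributed nothing to it. A real benefit in one tradition could also be diluted below detection. Because allocation is randomised within religion, each programme has its own concurrent same-religion waitlist. The comparison that addresses a tradition-specific claim will be in the data, but the article does not name it.

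**Working it through.** **1. The plan's own figure.** The Power analysis gives four groups, three timepoints, alpha 0.05, power 0.85, 10% dropout and an effect size of 0.1. The correlation between repeated measures is not given; I assume 0.5. For the group-by-time interaction, λ = f²·N·m/(1−ρ), with (k−1)(m−1) and (N−k)(m−1) degrees of freedom. With k = 4, m = 3 and f = 0.1, power 0.85 needs N = 260 (λ = 0.01×260×3/0.5 = 15.6). Then 260/0.9 = 288.9, or 289, against the stated 288. So 288 is reproduced when 0.1 is read as f. Read as f² (f = 0.316) it gives 32, or 36 with dropout. Correlations of 0.3 to 0.7 give 360 to 156 before dropout. Three conditions instead of four would give 228, or 254 with dropout. The sizing thus counts the programmes separately while the analysis sentence merges them. This is context; the results below do not depend on it.

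**2. Layout.** With 144 per religion and 72 per group, an even split of MBSR and waitlist gives 72 spiritual, 36 MBSR and 36 waitlist in each religion. The split is an assumption. Equal thirds (48:48:48) give the same variances, since 1/72 + 1/36 = 1/48 + 1/48.

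**3. Standard errors at full enrolment (SD = 1, unadjusted).**
- Pooled, 144 vs 72: √(1/144 + 1/72) = 0.144.
- Within one religion, 72 vs 36: √(1/72 + 1/36) = 0.204.
- Difference between the two within-religion contrasts (the interaction): √2 × 0.204 = 0.289.

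**4. One programme works (effect d), the other does nothing.** The pooled effect is (d + 0)/2 = d/2. The chance of a significant favourable result is Φ(effect/SE − 1.96). For d = 0.4 pooled: 0.2/0.144 = 1.39, and Φ(−0.57) = 0.28.

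| d (not in the documents; assumed) | Pooled test, one programme works | Pooled test, both work | Working programme vs own waitlist | Interaction, one programme works |
|---|---|---|---|---|
| 0.2 | 0.10 | 0.28 | 0.16 | 0.10 |
| 0.4 | 0.28 | 0.79 | 0.50 | 0.28 |
| 0.5 | 0.41 | 0.93 | 0.69 | 0.41 |

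The interaction column equals the first because d/0.289 = (d/2)/0.144. After 10% dropout the first column becomes 0.10, 0.26 and 0.38.

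**5. Precision of the within-religion contrasts after 10% dropout** (64.8 vs 32.4). SE = √(1/64.8 + 1/32.4) = 0.215. Adjusting for T1 with an assumed correlation of 0.5 multiplies this by √0.75, giving 0.186.
- 95% CI half-width: 1.96 × 0.215 = 0.42, or 1.96 × 0.186 = 0.37 SD.
- Detectable difference at 80% power: 2.80 × 0.215 = 0.60, or 2.80 × 0.186 = 0.52 SD.

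Charitable Giving is measured only at T2, so only the unadjusted ends (0.42 and 0.60) apply to it.

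**The case against.** The case for leaving the plan alone is substantial. The trial is described as three-arm, with two variants of one condition. Background and rationale explains why they form a class: a shared focus on the heart, shared aims and a shared emotional emphasis. Study interventions gives all programmes the same structure and duration. The hypotheses are at class level, so the pooled contrast tests what is hypothesised. All of this stands, and pooling is not an error.

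A reader might infer more: that the programmes will be tested only in pooled form, and that an ineffective one would be declared efficacious. The documents do not support that. The analysis text is one paragraph of a condensed article, the statistical analysis plan is not shown, and nothing rules out further contrasts. The concluding sentences in the Abstract and Discussion are conditional and set no decision rule.

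A reader might also reach for extreme cases. With 0.8 SD in one tradition and zero in the other, the pooled test is significant in 75% of trials after dropout without adjustment, or 86% with it. Effects of +0.4 and −0.4 SD cancel altogether. Neither case has a basis in the documents. The Power analysis plans for a small effect, and f = 0.1 corresponds to about d = 0.2 between two equal groups, where the chance is about 10%.

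It is also fair to say that an interaction test is weak here (0.10 to 0.41 for d = 0.2 to 0.5), and that two contrasts on each of the six primary measures in Table 2 add 12 estimates. This argues for presenting them as secondary estimates with intervals, not for omitting them.

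**Conclusion.** The point holds as a limit on what the stated comparison can show. The pooled contrast answers the class-level hypothesis. It does not by itself support a statement about either tradition, and the key question and concluding remarks are worded so that they can be read that way.

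At the small effects the trial plans for, the more frequent consequence is a missed one-tradition benefit. At d = 0.5 in one programme only, for example, the pooled test succeeds in 41% of trials, against 69% for that programme's own contrast.

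The figures rest on unit SD, a normal approximation to a two-group contrast (not the full MANOVA), the even waitlist split, and assumed values of d and of the T1 correlation. The pooled percentages are for full enrolment; the interval widths allow for 10% dropout. This is a worthwhile, inexpensive improvement and does not threaten the trial's validity.

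**What to change.** 1. Keep the pooled spiritual-minus-waitlist contrast as the main test and label it as the average of the two programmes.
2. Include religion, the stratification factor, and a condition-by-religion term in the model.
3. For each primary measure, report at T2 (the waitlist's last assessment) the Christian programme minus the Christian waitlist and the Islamic programme minus the Islamic waitlist. Give these as secondary estimates with 95% confidence intervals and the detectable difference of about 0.52 to 0.60 SD alongside. Do not use them as significance gates.
4. State that a non-significant interaction does not show equal effects, given its low power.
5. Word the Abstract and Discussion conclusions at class level unless a tradition's own contrast supports a claim for that tradition.

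The cost is analysis-plan wording and two contrasts per primary measure, fixed before the data are analysed. It needs no new participants or data and no change to randomisation. The downside is that the tradition-specific intervals will be wide, the added contrasts are not confirmatory, and the claim for each tradition may be weaker than the pooled one.

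### The analysis section names what read as condition and time main effects, and not the condition-by-time or baseline-adjusted T2 contrast that the hypothesis against the waitlist requires

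*Protocol article*

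**What the plan says.** The Quantitative data section fixes the model: "A series of mixed-design Repeated Measures Multivariate Analysis of Variance (RM-MANOVA) will be used". It then says what the model is for. The first purpose is to "test the mean difference in the outcomes among conditions (Spiritual meditation, mindfulness, and waitlist control groups) across T1, T2 and T3". The second follows directly: "as well as within participants across all time points (T1, T2 and T3". One exception is stated, for the prosociality variable "measured by Charitable Giving task, will be only compared between groups at T2". A p-value below 0.05 is the only criterion for significance.

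The hypotheses have two parts. The within-arm part begins "We hypothesise that when compared to baseline, individuals undertaking the heart-centred contemplative practices will show" and lists the expected improvements. The between-arm part is that "these outcomes will be greater for participants in the heart-centred contemplations compared to those in the waitlist control condition". For spiritual meditation against MBSR, no direction is predicted.

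The Power analysis section describes its calculation as "considering four groups with mixed method repeated measures at three timepoints". It uses an effect size of 0.1, alpha 0.05 and power 0.85, and reaches 288 participants after allowing for 10% dropout.

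The Primary outcomes section and Table 2 put the Dictator Game, Social Value Orientation (SVO), forgiveness and empathy at T1 and T2, perspective taking at T1, T2 and T3, and Charitable Giving at T2. The waitlist attends T1 and T2 only.

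**The concern.** In a mixed design, a mean difference among conditions across visits is most directly the between-subject main effect, and a difference within participants over visits is the time main effect. Neither asks whether the arms changed by different amounts, which is what the hypothesis against the waitlist asserts.

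Each has its own fault as a treatment test. T1 comes before treatment (the first meditation session starts at the end of the T1 assessment), so randomisation makes the expected arm difference there zero. A condition main effect that includes T1 dilutes the T2 effect and carries part of any chance imbalance at T1. The time effect pools the arms, so it mixes treatment with practice effects and drift.

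The stake is pre-specification. The fitted model will offer condition, time and condition-by-time terms, and the text designates only the first two. A null condition effect could then hide a real benefit, or a significant pooled time effect could be presented as efficacy.

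**Working it through.** **1. The plan's own figure.** From the Power analysis section: k = 4 groups, m = 3 time points, alpha 0.05, power 0.85, effect 0.1, dropout 10%. Assumed because not stated: correlation ρ = 0.5 between visits, and sphericity. The 0.1 is labelled f², but the total reproduces only if it is read as Cohen's f. Noncentral F:

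- Group-by-time interaction: λ = N f² m/(1 − ρ), with (k − 1)(m − 1) = 6 and (N − k)(m − 1) degrees of freedom.
- Between-group effect: λ = N f² m/[1 + (m − 1)ρ], with k − 1 = 3 and N − k degrees of freedom.

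| Test | Completers for 85% power | Divided by 0.9 |
|---|---|---|
| Group-by-time | 258 (260 in four equal groups) | 287 (289) |
| Between groups | 824 | 916 |
| Time | 184 | 205 |

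Conversely, 288 × 0.9 = 259.2. Only the interaction comes close to 288. With f² = 0.1 (f = 0.316), the interaction would need only 32 completers.

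**2. What a condition main effect would estimate.** Take an outcome measured at T1 and T2, with no expected arm difference at T1 and a difference d at T2, in units of the common SD. The main effect estimates (0 + d)/2 = d/2. A simulation (4,000 runs, both meditation arms given the effect) returned 0.20 for d = 0.4 and 0.25 for d = 0.5.

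For an outcome at all three visits the factor would be 1/3 if the effect is present at T2 only, and 2/3 if it persists to T3. The waitlist has no T3 value to include.

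**3. Power for the two-visit outcomes.** Assumed: equal allocation to three conditions, so 288/3 = 96 per arm, less 10% ≈ 86 completers; and equal variances. The SD of the quantity compared is

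- mean of T1 and T2: √[(1 + ρ)/2], with effect d/2;
- change from T1 to T2: √[2(1 − ρ)], with effect d;
- T2 adjusted for T1: √(1 − ρ²), with effect d.

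Power ≈ Φ(effect/SD × √(86/2) − 1.96). For example, with d = 0.5 and ρ = 0.5:

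- main effect: 0.25/0.866 × 6.557 = 1.893, and Φ(−0.067) = 47%;
- change: 0.5/1 × 6.557 = 3.279, and Φ(1.319) = 91%.

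| d | Test | ρ = 0.3 | ρ = 0.5 | ρ = 0.7 |
|---|---|---|---|---|
| 0.5 | Condition main effect | 53% | 47% | 43% |
| 0.5 | Condition-by-time (change) | 79% | 91% | 99% |
| 0.5 | T2 adjusted for T1 | 93% | 97% | 99.6% |
| 0.4 | Condition main effect | 37% | 33% | 30% |
| 0.4 | Condition-by-time (change) | 60% | 75% | 92% |
| 0.4 | T2 adjusted for T1 | 79% | 86% | 96% |

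Using the t distribution instead of the normal moves these by less than one percentage point. The simulated three-arm F tests agree: for d = 0.5, 55%, 49% and 43% for the main effect against 82%, 93% and 99% for condition-by-time.

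**The case against.** The best defence is that the sentence is loose and does not fix a wrong test. It does not say that the visits are averaged. A mean difference among conditions across time points can also describe how the conditions differ over time. A mixed-design repeated-measures MANOVA yields the interaction as standard, and the hypotheses and sample size both fit it. This is also a journal article, and the exact model term and contrast may be given in an analysis plan not shown. All of this stands as an argument about intent. It does not remove the point, because the article goes beyond leaving the tests open: it lists two and omits the one that its between-arm hypothesis needs.

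A reader might go further and infer that the trial will test a visit-averaged main effect, with power falling from 85% to 34% and 824 completers needed. The documents do not support this. No passage designates the main effect as the treatment test. The 34% (at 259 completers) and the 824 also put f = 0.1 into both tests, whereas one treatment effect would not give the same f in each. Take an interaction f of 0.1 at correlation 0.5. An effect absent at T1 and equal at T2 and T3 makes the main-effect f 1.41 times as large, with about 63% power. An effect at T2 only makes it 0.71 times as large, with about 19%.

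Nor is halving general. It applies to the T1/T2 outcomes, not to perspective taking or the three-visit mental health scales, and not to Charitable Giving.

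**Conclusion.** The point holds as a failure to name the treatment test. Taken literally, the analysis section describes condition and time main effects. Neither tests whether improvement exceeds that in the waitlist, and no other section supplies the contrast that would. The sample size suggests that the interaction was intended, subject to the assumed correlation of 0.5 and reading 0.1 as Cohen's f. The documents therefore do not show that the wrong test will be run; they leave that possible.

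The cost if it were run is conditional but large. For the Dictator Game, SVO, forgiveness and empathy, the estimate would be half the T2 effect. With d = 0.5, power would be 43% to 53% where condition-by-time has 79% to 99%, over correlations of 0.3 to 0.7. This rests on 86 completers per arm, equal variances and no expected T1 difference. The effect size and correlations are illustrative, since the protocol gives neither on this scale.

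**What to change.** Replace the description of the tests with wording such as: *For outcomes measured at T1 and later, the test of the intervention effect is the spiritual-minus-waitlist difference at T2, adjusted for the T1 value (or the equivalent condition-by-time contrast). The condition main effect over visits and the pooled time effect are not tests of the between-arm hypothesis. Charitable Giving is compared between conditions at T2 only.*

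The adjusted form is preferable. Under randomisation it targets the same T2 difference as the change contrast, and its variance is 1 − ρ² against 2(1 − ρ), a ratio of (1 + ρ)/2. It also corrects for chance imbalance at T1.

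The cost is about one sentence in the analysis section, settled before the data are analysed. The T1 and T2 measurements are already scheduled, so no new data or participants are needed. If the interaction was always intended, nothing changes except that the plan says so.
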